## Abstract

**Background:**

As the histopathology workforce continues to struggle and service demand continues to increase, it has become prudent to consider viable avenues to try to alleviate diagnostic workload burden. One such avenue is computer-based technologies (CBTs). Breast cancer (BC) is the most common malignant neoplasm in the United Kingdom and requires additional testing for estrogen receptor (ER), progesterone receptor (PR), and human epidermal growth factor receptor-2 (HER2) status at the time of histological diagnosis. This makes BC diagnostics a promising candidate for the application of an efficient CBT. However, for clinical acceptance, these technologies must prove that they work within a real-life diagnostic environment.

**Objective:**

We present a study protocol for a prospective clinical service evaluation aimed to validate a UK Conformity Assessed–marked CBT’s ability to provide ER, PR, and HER2 results for invasive BCs from scanned hematoxylin and eosin-stained whole slide images.

**Methods:**

This protocol has been designed to use and mimic a preexisting digital pathology workflow within a National Health Service tertiary referral cancer center without disrupting normal patient care. Eligible cases are identified prospectively through the laboratory information management system, and their whole slide images are extracted from the clinical digital workflow. After verification of national data opt-out status and the exclusion of appropriate cases (N=400 analyzable cases), these cases are analyzed on a dedicated computer in parallel to the existing clinical workflow by a UK Conformity Assessed–marked deep learning–based CBT in a separate environment, providing results for ER, PR, and HER2 status. These results are compared to the ER, PR, and HER2 status reported on the corresponding pathology report. To evaluate the CBT’s performance, a range of accepted concordance measures will be applied, including specificity, sensitivity, false-positive rate, false-negative rate, positive predictive value, and negative predictive value. Moreover, time stamps representing the duration of image analysis will also be collected.

**Results:**

This study started in April 2025. There are no results to present, as this paper focuses on study design, and results have yet to be generated. As of March 2026, overall, 366 potentially analyzable cases have been collected. The anticipated end date of the study is May 2026 (400-case target). Results will be presented in a separate publication.

**Conclusions:**

This design assesses a CBT within a clinical environment while effectively eliminating any unwanted effects on patient care. This type of service evaluation provides a useful step to establish confidence in a CBT before trialing its effect on patient care. It also offers the opportunity to support interventional randomized controlled trials, health economic evaluations, and usability studies. This protocol will hopefully prove useful to others who wish to conduct a similar service evaluation at their own institution.

**International Registered Report Identifier (IRRID):**

DERR1-10.2196/76785

## Introduction

It is now well recognized that the histopathology workforce, both in the United Kingdom and globally, is in crisis [1]. The UK Royal College of Pathologists’ 2018 workforce census revealed that only 3% of departments were sufficiently staffed to meet clinical need [2]. The report also highlighted that a quarter of histopathologists were older than 55 years, and the workforce in England would fall to 74% of its current level if all these pathologists were to retire within 5 years. Additionally, the census estimated that there is a UK-wide £27 million (CAD $50.09 million=US $36.68 million) annual spend compensating for staffing shortfalls through locums and outsourcing work. The census also acknowledged the increasing use of additional molecular and genomic testing in diagnostic work. This predicament is exacerbated by the increasing cancer burden. In this respect, Cancer Research UK reported that more than 385,000 new cancers were diagnosed annually in the United Kingdom between 2017 and 2019 [3]. This is predicted to increase to approximately 506,000 by 2038 to 2040 [4]. This increase would place unparalleled pressure on an already stretched histopathology service, potentially affecting patient care.

Digital pathology is an area that the Royal College of Pathologists has acknowledged could help alleviate this problem by enabling more efficient working [2]. In fact, pathology departments throughout the United Kingdom are starting to digitize, creating an opportunity to explore the merit of adjunct computer-based technologies (CBTs). These could lighten the workload of both pathologists and pathology departments by replacing or assisting with time-consuming tasks. For example, the first and currently only Food and Drug Administration–approved artificial intelligence (AI)–based pathology software Paige Prostate [5] can aid pathologists by highlighting areas suspicious for carcinoma in prostate biopsies [6-8], apparently reducing a pathologist’s review time of a full set of cases by 65.5% [6]. In fact, a service evaluation, the Artificial Intelligence for Cellular Pathology Transformation in Prostate Practice project based in Oxford, United Kingdom, has been conducted to assess the use of Paige Prostate, helping histopathologists with prostate biopsy evaluation [9,10].

Another common malignant tumor where time savings could be invaluable is breast cancer (BC). In the United Kingdom, data from 2017 to 2019 showed that BC was the most common malignancy seen in the country over that period [11]. Additionally, all newly diagnosed invasive BCs in the United Kingdom undergo testing for estrogen receptor (ER), progesterone receptor (PR), and human epidermal growth factor receptor-2 (HER2) status to determine molecular subtype and guide treatment [12]. ER and PR testing involves immunohistochemistry [12], while HER2 testing requires immunohistochemistry with or without in situ hybridization (ISH) [13]. These ancillary tests generate more work and cost for histopathology laboratories in terms of specimen preparation and staining as well as commandeering pathologists’ time to score and report the results. In this setting, any technology that could alleviate this time burden would be welcome. This would be particularly beneficial if it could extract such diagnostic information from hematoxylin and eosin (H&E)–stained whole slide images (WSIs) alone, as H&E-stained tissue interpretation is already the first, essential step in a pathologist’s diagnostic assessment. Akin to Paige Prostate, the technology company Ibex has been awarded UK-based funding to trial its BC diagnostic platform in a number of UK hospitals [14], although this technology focuses on BC detection on H&E-stained WSIs rather than molecular subtype profiling [15].

While CBTs have become an attractive area for research scientists and manufacturers, no such technology has translated into the active clinical space in the United Kingdom. The underlying reasons are multifaceted, including the need for significant validation [16,17], cost implications [16-18], and the lack of defined minimal performance levels acceptable to pathologists [17]. It has been proposed that, ideally, robust validation for CBTs requires a multicenter clinical trial with a cost-benefit analysis [16]. In this regard, the United Kingdom’s National Cancer Research Institute Cellular Molecular Pathology Initiative and the British In Vitro Diagnostics Association published a road map for bringing AI into routine clinical pathology practice [19]. This recommends that a trial akin to phase I (analytic validation) and phase 2/3 (clinical validation) in drug development be carried out to facilitate the regulatory approval and clinical use of these technologies. In addition, they describe phase I studies as including a health economic assessment. Furthermore, they provide a study comparing a tool for grading Ki-67 in neuroendocrine tumors entering a department during a set time frame with pathologists as an example of a “clinical (phase 2/3) validation”.

To help bridge the gap between development and clinical adoption, we have designed a protocol for a prospective clinical service evaluation of a UK Conformity Assessed (UKCA)–marked CBT implemented within digital pathology. This study evaluates a CBT’s ability to provide the molecular subtype (ER, PR, and HER2 status) of invasive BCs on biopsy specimens within an operational, digitized histopathology department. This evaluation has been purposefully designed to run alongside routine diagnostic practice and not interfere with patient management. This ensures that the CBT can be assessed in a clinical environment without direct impact on patients. We believe that this is an essential step to build confidence in these technologies before they are used to inform patient care. The CBT to be tested in our specific study is the UKCA-marked, deep-learning technology PANProfiler Breast (Panakeia Technologies Limited).

The design of this service evaluation is shared herein to provide other investigators with a reference point to conduct other similar studies to help bring CBTs into the digital pathology space. The aim of this service evaluation is to validate the technology’s performance in the molecular subtyping of invasive BCs from H&E WSIs of BC biopsy specimens in a real-life clinical environment.

## Methods

### Service Evaluation Design and Setting

This service evaluation has been designed to be carried out within a pathology department with a pre-established digitized workflow. Our study will take place at St James’s University Hospital, Leeds Teaching Hospitals National Health Service (NHS) Trust (LTHT), United Kingdom. We have attempted to simulate how a CBT could integrate into the journey of a breast biopsy specimen suspicious for malignancy through this specific digital workflow. As mentioned, this evaluation is noninterventionist and runs parallel to the existing clinical pathway. It avoids interrupting or affecting laboratory processes, clinical reporting, or patient management. The generic steps of this clinical service evaluation are presented in Figure 1. To ensure minimal disruption to clinical services, all trial work will be conducted by a dedicated research team.

**Figure 1 figure1:**
[figure not shown]
Demonstration of the clinical service evaluation design and its integration into a digital pathology workflow. (A) Steps in the routine digital pathology workflow. General specimen processing and reporting are shown in white. Handling of digital images is shown in green. Centralized digital systems are shown in blue. (B) Steps in the clinical service evaluation. CBT: computer-based technology; LIMS: laboratory information management system; PACS: picture archiving and communication system; SAM: server application monitor; WSI: whole slide image.

### Identification of Cases

Eligible cases (N=400) will be identified prospectively as they are logged in at the histopathology department. At LTHT, cases are routinely assigned a unique Trust-specific specimen number and categorized using the local laboratory information management system (LIMS) codes. Breast biopsies that are suspicious for malignancy at the time of sampling are assigned one of a set of specific LIMS codes. Researchers will search the LIMS using this set of specific codes to identify eligible cases (Figure 2). Generic inclusion criteria include all patients with a breast biopsy specimen processed at St James’s University Hospital. Exclusion criteria are samples in line with the device’s indications for use. These include (but are not limited to) noncarcinoma malignancies (eg, angiosarcomas), malignancies not arising from breast tissue (eg, cutaneous carcinomas arising from breast skin), and those confirmed not to have invasive malignancy. These exclusions will be performed at the time of data collection from pathology reports. Applying these criteria, convenience sampling will be used to (1) simulate the histopathology workflow as closely as possible and (2) ensure that all relevant or eligible cases are captured during the study period. When identified, the case’s specimen number and NHS number will be collected, and a unique, anonymized study number will be allocated. The digital WSIs for a case will also be extracted (refer to the Extraction of Digital Images section), and an anonymized image number will be assigned that is aligned with the corresponding study number.

**Figure 2 figure2:**
[figure not shown]
Data handling through the clinical service evaluation. CBT: computer-based technology; LIMS: laboratory information management system; NHS: National Health Service; WSI: whole slide image.

### Extraction of Digital Images

Once all potential cases are identified for the service evaluation, their images will be extracted and saved securely on the Trust’s IT storage (Figures 1-2). This design uses WSIs scanned as part of a histopathology department’s pre-established workflow (Figure 2). Briefly, researchers will manually access and duplicate relevant WSIs, saving them on the Trust’s secure IT server. Images will be anonymized using an SVS-deidentifier tool (Pearcetm); licensed by the Massachusetts Institute of Technology), which removes patient metadata without affecting the WSI. To remove the Trust-specific specimen number, researchers will manually rename the image files with the unique, anonymized image number assigned to the case.

### NHS National Data Opt-Out Checks

After the identification of eligible cases and corresponding image extraction, National Data Opt-Out Scheme (NDOS) checks will be completed (Figure 2). The NHS England NDOS offers patients the option to opt out of their data being used for research [20]. At LTHT, the Research Data and Informatics Team (R-DIT) will perform NDOS checks to ensure patients who have opted out are identified and have their wishes honored. To perform these checks, R-DIT requires patient NHS numbers. The research team will securely transfer the NHS numbers of the samples identified for the service evaluation to the R-DIT. R-DIT will then inform the research team which cases can or cannot be included in the study. All cases that have opted out will have all data and images collected up to that point deleted. Additionally, the NHS numbers for all cases will be deleted as they will no longer be required.

### Data Collection From Pathology Reports

To determine the accuracy of the CBT, researchers will collect ER, PR, and HER2 data from authorized pathology reports (Figure 2). The cases that are subsequently excluded because of NDOS compliance will have their data deleted before any analysis. At LTHT, breast specimens are reported by breast subspecialist histopathologists, and the results reported for ER, PR, and HER2 status in these reports will be used as the ground truth. This data collection will take place before the CBT results are generated by the research team and will not be shared with the technology providers. This keeps the evaluation fully blind. For completeness, the type of specimen will also be collected, for example, core biopsy or vacuum-assisted biopsy. Once this information has been collected from the pathology reports, the specimen numbers for all cases will be deleted. This removes any link back to the patient, which is particularly important when starting to analyze the CBT’s performance.

### Transfer of Anonymized Digital Images to a Dedicated Workstation

A dedicated desktop PC will be established to run the CBT. The CBT will be installed before eligible samples are identified. Once set up, the anonymized WSIs will be uploaded to this dedicated desktop via 256-bit encrypted keypad external hard drives and stored securely (Figures 1-2). This desktop will be located within the NHS Trust intranet; however, it will not be connected to the LIMS or the electronic patient record system. This will help ensure there is no crossover between the service evaluation and standard patient care.

### The CBT To Be Evaluated

The CBT to be used in this service evaluation is PANProfiler Breast, a UKCA-marked, deep learning-based technology that leverages computational methods to analyze H&E-stained BC WSIs. Specifically, it extracts histomorphological features associated with ER and PR expressions as well as HER2 status. This has been described in detail elsewhere [21].

### The CBT’s Analysis of Anonymized Digital Images

Once the anonymized WSIs have been uploaded to the dedicated PC, the research team will use the CBT and analyze the images (Figures 1-2). This will generate results for ER, PR, and HER2 status, and these will be recorded by the researchers. Time stamps pertaining to the time and date of file upload and the generation of results following image analysis will also be collected. ER, PR, and HER2 results will be compared to the ground truth. This image analysis will only be conducted after the data from the corresponding pathology report have been collected and the specimen number deleted. Because we do not intend to influence patient care, we prevented the CBT results from linking back to the patient in this way. After the image analysis has been completed for a case, the images will be deleted from all hard drives. This approach ensures adherence to Trust Information Governance requirements and prevents the images from being mistakenly analyzed more than once.

### Data Analysis

To validate the CBT’s diagnostic accuracy in this clinical service evaluation, concordance will be established with the ground truth (ie, the pathology report). Measures including sensitivity; specificity; false-positive rates and false-negative rates; and positive and negative predictive values for ER, PR, and HER2 will be calculated based on the formulae presented in Table 1. The time difference between the 2 time stamps collected will also be calculated. From this, a range and median time for the CBT’s result generation will be quantified.

**Table 1 table1:** The standard diagnostic metrics used to measure the performance of PANProfiler Breast.

Performance metric	Definition
Concordance	Number of concordant cases/total number of cases with definitive PANProfiler result
Sensitivity	TP^a^/TP+FN^b^
Specificity^c,d^	TN^c^/TN_FP^d^
Positive predictive value	TP/TP+FP
Negative predictive value	TN/TN+FN
False-negative rate	FN/TP+FN
False-positive rate	FP/TN+FP
Test replacement rate	Number of cases with definitive PANProfiler result^e^/total number of cases
Complete test replacement rate	Number of cases with definitive PANProfiler results*for all marks/total number of cases

^a^TP: true positive.

^b^FN: false negative.

^c^TN: true negative.

^d^FP: false positive.

^e^Definitive PANProfiler result for HER2 is “negative,” and definitive PANProfiler result for estrogen receptor or progesterone receptor is “positive” or “negative.” The table is taken from the supplementary material of our previous publication [21].

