## Results

The study started in April 2025. There are no results to present to date, as this paper is focused on study design, and final results have yet to be generated. As of March 2026, 366 potentially analyzable cases have been collected, and the anticipated end date is May 2026. This study will be considered complete once the target 400 cases have been analyzed. Given the prospective nature of this study, the duration/achieving this target will depend on the variability of routine clinical throughput. The results of this evaluation will be the subject of a separate publication in which any deviation from this protocol will be described, as appropriate.

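### For ER and PR, Table 1 scores accuracy only among definitive CBT results and does not split the replacement rate by reference class, so it can overstate how often a case gets a correct answer

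*Protocol article*

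**What the plan says.** The Data Analysis section of the protocol article says that the accuracy measures "for ER, PR, and HER2 will be calculated based on the formulae presented in Table 1". In that table:

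- Concordance is "Number of concordant cases/total number of cases with definitive PANProfiler result".
- Sensitivity, specificity, false-negative rate and false-positive rate are ratios of TP, FN, TN and FP only.
- The test replacement rate is "Number of cases with definitive PANProfiler result^e^/total number of cases". A complete test replacement rate, for all markers together, has the same denominator.
- Footnote e says that a "definitive PANProfiler result for estrogen receptor or progesterone receptor is" positive or negative. For HER2, only a negative result is definitive.

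Under Data Collection From Pathology Reports, "the results reported for ER, PR, and HER2 status in these reports will be used as the ground truth". Every case scored on a marker therefore has a reference class, whether or not the CBT gives a definitive answer. Identification of Cases describes sampling meant to "ensure that all relevant or eligible cases are captured during the study period". Under Results, "This study will be considered complete once the target 400 cases have been analyzed". The article gives no expected non-definitive rate, receptor prevalence or accuracy target.

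**The concern.** Footnote e and the replacement rate make sense only if the CBT can return something other than positive or negative for ER and PR. Such a case has no place among TP, FN, TN and FP, so it drops out of sensitivity and specificity. The concordance row states its restriction in words. The sensitivity and specificity rows do not.

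The stated aim is performance in a real clinical environment, and the Discussion considers an economic comparison in which the CBT replaces immunohistochemistry. For those uses the reader needs to know how often a receptor-negative cancer, and separately a receptor-positive one, receives a correct answer. That depends on how often the CBT answers within each class, which Table 1 does not ask for. A replacement rate over all cases shows how many non-answers there are, but not in which class they fall.

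**Working it through.** The article states no accuracy figure, so there is none to reproduce. The check is table arithmetic.

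**Inputs.** From the article: 400 cases and the Table 1 formulae (specificity read as TN/(TN+FP)). Assumed, not from the article: 80% reference-positive (320 positive, 80 negative), replacement rate 90% (360 definitive, 40 non-definitive), sensitivity 95% and specificity 85% among definitive results.

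**Formulae.** Counting a non-definitive result as not correctly classified:

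- all-case concordance = (TP+TN)/400 = Table 1 concordance × replacement rate;
- all-case sensitivity = TP/(all reference-positive) = Table 1 sensitivity × definitive rate among reference-positive cases;
- all-case specificity = TN/(all reference-negative) = Table 1 specificity × definitive rate among reference-negative cases.

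**Three ways to place the same 40 non-answers.**

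| Non-answers | TP | TN | Sensitivity, all cases | Specificity, all cases | Concordance, definitive → all |
|---|---|---|---|---|---|
| all 40 negative | 0.95×320 = 304 | 0.85×40 = 34 | 304/320 = 0.950 | 34/80 = 0.425 | 338/360 = 0.939 → 338/400 = 0.845 |
| all 40 positive | 0.95×280 = 266 | 0.85×80 = 68 | 266/320 = 0.831 | 68/80 = 0.850 | 334/360 = 0.928 → 334/400 = 0.835 |
| 32 positive, 8 negative | 0.95×288 = 273.6 | 0.85×72 = 61.2 | 273.6/320 = 0.855 | 61.2/80 = 0.765 | 334.8/360 = 0.930 → 334.8/400 = 0.837 |

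All three rows have the same Table 1 sensitivity, specificity and replacement rate. The lowest sensitivity and the lowest specificity cannot occur together, because the 40 non-answers are shared between the classes.

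**Dependence on the assumed prevalence.** With 40 non-answers all reference-negative, all-case specificity is 0.85×80/120 = 0.567 at 70% positive and 0.85×20/60 = 0.283 at 85% positive. Over prevalence 70%, 80% or 85%, replacement rate 60%, 75% or 90%, and three placements of the non-answers, all-case concordance runs from 0.54 to 0.85, against 0.90 to 0.95 among definitive results.

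**What can be recovered.** All-case concordance can: 0.930 × 0.90 = 0.837. For sensitivity and specificity, Table 1 gives the class mix of the definitive cases only. In the first row, (0.939 − 0.85)/(0.95 − 0.85) ≈ 0.889 = 320/360. Turning that into a definitive rate per class also needs the numbers of reference-positive and reference-negative cases among all 400, which Table 1 does not list.

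**What does not change.** PPV and NPV condition on a positive or negative call, so non-answers enter neither numerator nor denominator. A non-answer is also not a wrong answer. In the second row FN = 14, which is 14/280 = 5.0% of definitive and 14/320 = 4.4% of all reference-positive cases. What can be overstated is the share correctly answered. The share wrongly answered is not understated.

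**The case against.** Accuracy given an answer, paired with the rate of answering, is a legitimate way to report a test that may abstain. Table 1 plans that pair, with "total number of cases" as the replacement-rate denominator, so abstention is disclosed and a device that abstains more would show a lower replacement rate. Counting a non-answer as not correct is a different estimand and does not correct an error. A results paper may well show the cross-tabulation, or at least the class totals that would allow the missing rates to be worked out. All of this stands, and it is why the conditional figures should stay. It does not fill the gap: the formulae are stated rules, and neither the class-specific rates nor the class totals are among them.

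Three stronger readings are tempting.

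- A reader might infer that ER and PR performance is overstated as a matter of fact. There are no results and no non-definitive rate. The direction also depends on how non-answers are scored: with all 40 in the negative class, specificity is 34/80 = 0.425 if they count as wrong and (34+40)/80 = 0.925 if they count as right, against 0.850 among definitive results.
- A reader might infer that non-answers gather in difficult cases or in the smaller class. The article says nothing on this. The point is that Table 1 would not show whether they do.
- A reader might extend the all-case rule to every marker. For HER2 only a negative result is definitive, so all-case sensitivity would be zero by construction.

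**Conclusion.** The point holds for ER and PR as a limit on what the planned metrics can show. Concordance, sensitivity, specificity and the false-negative and false-positive rates are conditional on a definitive result, and only concordance says so. They can overstate how often a case in the tested population gets a correct answer. All-case sensitivity and specificity do not follow from the listed metrics.

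The size cannot be taken from the article. In the illustration, one set of conditional figures and one replacement rate is compatible with all-case specificity from 42.5% to 85% and sensitivity from 83% to 95%. This rests on the assumed prevalence, replacement rate and conditional accuracy, and on counting non-answers as not correctly classified. If the CBT answers in nearly every case, the difference is negligible. It is worth settling now, because the article reports that results have yet to be generated.

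**What to change.** For ER and PR:

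1. Label the Table 1 concordance, sensitivity, specificity, false-negative rate and false-positive rate as *among definitive results* wherever they are quoted.
2. Publish the two-by-three table: CBT positive, negative or non-definitive, by reference positive or negative.
3. Report the definitive rate separately for reference-positive and reference-negative cases.
4. Report all-case sensitivity and specificity beside the conditional values, with non-definitive counted as not correctly classified.

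For HER2, report the CBT output by reference class and the definitive (negative) rate in each class. Do not apply the all-case sensitivity rule.

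The cost is a few extra table rows, from results that the researchers already record, and a less favourable figure next to the headline accuracy. Because images are deleted after each case is analysed, the non-definitive output must be logged per marker at the time of the run.
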